#### (B) Secondary Objective Analysis Plan

Summative statistics will be used to describe the distribution of responses to closed-ended questions. Answers to open-ended questions will be thematically coded; concepts and themes will be developed using a constant comparative method of analysis. Themes related to knowledge of pain and analgesia, fears of AEs or effectiveness of analgesia, satisfaction or dissatisfaction with current therapy will be categorized, among others. Survey findings will not be included in the primary or secondary outcome analyses and will be presented separately as an exploratory component of the study.

### Planned Subgroups

There are 5 planned subgroups:

(1) Underlying painful condition, specifically the 2 most common indications for IV ketorolac, headaches, and acute abdominal pain. No subgroup effect is anticipated given evidence that the cause of pain does not alter response to analgesia [35,36].

(2) Age ≥12 years, since adolescents’ drug metabolism differs from younger age groups. We expect a differential treatment effect but are uncertain regarding direction or magnitude.

(3) Gender (grouped as cisgender, transgender, and other): since gender norms are known to impact a patient’s perceived sensitivity to pain, we will advise participants and caregivers why sex and gender are important in pain research and then use the recommended [37] 2-step questionnaire to determine biological sex and gender separately. The 2-step survey has been tested in transgender populations and validated over a broader North American population [38-42]. We expect a differential treatment effect but are uncertain regarding direction or magnitude.

(4) Sex (male, female, and intersex): since biological mechanisms, such as sex hormones, influence the nervous system’s perception of pain and response to analgesics [43-45]. We expect a differential treatment effect but are uncertain regarding direction or magnitude.

(5) Race and ethnicity: we will collect race and ethnicity data using the standard Canadian Institute for Health Information data questionnaire, with 2 questions on Indigenous identity data standard and race-based data standard [46]. We expect a differential treatment effect but are uncertain regarding direction or magnitude (see Table 1).

**Table 1 table1:** Summary of outcomes and analysis.

Objectives				Outcome measure		Hypothesis		Analysis			
**Primary efficacy outcome^a^**											
		Pain relief		Pain level as reported by participants on an 11-point vNRS^b^ score at 60 minutes post administration of trial drugs.		Ketorolac given at 0.5 mg/kg/dose up to 10 mg or at 0.25 mg/kg/dose up to 30 mg will be noninferior to standard dose ketorolac		Intention to treat analysis using ANCOVA^c^			
**Safety outcome**											
		Group differences in proportion of AEs^d^		The proportion of children experiencing AEs related to study drug administration		Participants who receive low dose will have fewer AEs than those who receive standard dose		Regression analysis			
**Secondary outcomes**											
		**Efficacy**									
			Pain relief at all time points		Between group differences in pain score at all study time points at 30, 90 and120 minutes		Low dose will be noninferior to standard dose at all time points.		GEE^e^: adjusted for baseline pain scores		
			Pain relief by the MID		Proportion who achieves a 2-point vNRS reduction at 60 and 120 minutes		Low dose will be noninferior to standard dose ketorolac regimens in reducing pain by the 2-point MID^f^ on vNRS		Regression analysis		
			Pain category change		Proportion of participants who change their baseline pain category at all time points (mild 1 to 3, moderate 4 to 6, severe ≥7 on vNRS)		No difference between low dose and standard dose ketorolac in pain category change at all time points		Regression analysis		
			Time to achieve mild or no pain level		Time to effective analgesia as measured by the time when vNRS of <3 is achieved		No difference between all ketorolac dosing arms.		Cox regression analysis		
			Rescue analgesia		Proportion of participants requiring any additional analgesia in each trial arm		No difference between all ketorolac dosing arms		Regression analysis		
			Opioid sparring		Total amount of opioid administered within 8 hours of intervention		No difference between all ketorolac dosing arms		Regression analysis		

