### Randomization and Participant Allocation

The study’s research pharmacist at McMaster Children’s Hospital research pharmacy will create a simple computer-generated block randomization list using Robust Randomization App [29] (Center for Biostatistics, Icahn School of Medicine at Mount Sinai) with random varying permutated blocks of 3, 6, and 9 and a 1:1:1 allocation ratio. The research pharmacists will prepare consecutively numbered study drug vials according to the randomization schedule, with clear labels and dosing instructions in each kit. At least 3 study drug kits will be stored in the password-protected ED medication dispensing machines as per standard operating procedures and Division 5 Good Clinical Practice Health Canada Guidelines. Drug kits will be replenished as needed (at a minimum, weekly) by the research pharmacists. Only the research pharmacists will retain the randomization codes.

A log of all screened patients will be maintained. If patients are eligible, details of the study will be discussed with patients and their caregiver. Consent and assent will be obtained as per the Hamilton integrated Research Ethics Board (HiREB) guidelines and approved consenting procedures (see Multimedia Appendix 3 for consent forms). The clinical research assistant will collect baseline clinical variables and will complete the data collection forms. Elements of baseline pain severity (assessed by vNRS), type of pain, location of pain, duration of pain since onset, associated symptoms (eg, nausea, anorexia, vomiting, dysuria, fever, and pain with movement) will be collected. The Clinical Research Assistant will then pick the next consecutively numbered drug kit and enter the drug kit coded number into Research Electronic Data Capture (REDCap; Vanderbilt University). The research nurse will administer the study drugs to the patient (ketorolac and placebo normal saline) according to the dosing guidelines as an IV push over 5 minutes. Five minutes is a safe timeframe to administer IV ketorolac. This is consistent with the instructions on the clinical drug monograph at our hospital. Time 0 will be defined as the point at which administration of the study drug is completed.

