### Duration of Treatment and Follow-Up

Ketorolac and a placebo can be given as an IV slow push over 5 minutes with or without a drug pump. Only a single dose will be administered as part of the trial. The effects on pain will be monitored by obtaining baseline pain scores with the vNRS and at times 30, 60, 90, 120 minutes, and at 6 hours if they are still in the hospital. At follow-up, ED and inpatient chart reviews will be completed to determine results of investigations, AEs, total doses of opioids administered in morphine equivalents/kg, all types of NSAIDs administered, dose and frequency for each and the final diagnosis assigned. The survey will be completed within 7 to 14 days once all clinical outcomes are completed (6 hours postintervention).

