#### Secondary Endpoints

Secondary endpoints include the following:

vNRS score at 30, 90, and 120 minutes as well as 6 hours post administration.Proportion of participants who achieve the 2-point vNRS MID pain score reduction at 60 and 120 minutes.Proportion of participants who change the severity of their baseline pain category at all time points (mild = 0 to 3, moderate = 4 to 6, severe ≥7 on the vNRS)[24].Time to effective analgesia (ie, time at which a vNRS <3 is achieved postintervention).Proportion of participants requiring any rescue analgesia in each trial arm.Total amount administered as measured by morphine equivalent mg/kg within 8 hours of intervention.

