### Analysis Plan

#### (A) Primary Objective Analysis Plan

Data will be described in terms of mean (SD) or 95% confidence limits for normally distributed data and frequency (percentage) in the case of categorical data. The primary endpoint is the difference between the mean reduction in pain scores between each of the low-dose groups (B1, B2) and the standard-dose group (A) 60 minutes post intervention. The primary analysis will include all participants randomized based on the intention to treat analysis and a sensitivity per-protocol analysis will also be performed. A priori, the primary analysis will be adjusted for baseline pain scores using the analysis of covariance (ANCOVA)*.* Generalized estimating equations will be used to examine the impact of baseline pain score on vNRS outcomes across the entire time frame. Noninferiority would be shown if the lower limit of the 95% CI for the between group (groups B1vs A or B2 vs A) differences in the primary endpoint is >1.0. If >5% [34] of our vNRS scores are missing within 120 minutes, we will use multiple imputation to create 5 datasets wherein any missing pain data will be imputed with the Markov chain Monte Carlo method. For secondary endpoints, we will describe those outcomes using descriptive statistics and perform a linear (continuous), logistic, or ordinal regression (categorical or ordinal). If both low-dose strategies are shown to be noninferior to standard dose, we will conduct an exploratory analysis to see if one low-dosing strategy is superior to the other (group B1 vs B2). This will be conducted using ANCOVA to adjust for baseline pain scores and superiority will be determined by a difference that is defined by the MID of 2.0 on the 11-point vNRS. All analyses will be conducted in a blinded fashion. The research pharmacist will provide the trial statistician with anonymized group allocation codes, without revealing the dosing strategies associated with each group. The group identities will remain blinded to the statistician until the first draft of the manuscript with results has been completed. All analyses will be done using SAS (version 9.4; SAS Inc).

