### Trial Day-to-Day Operations

A study coordinator with experience in Health Canada drug trials will work with principal investigators ([name]). Clinical Research Assistants and research nurses will be available to recruit from 8 AM to 9 PM. We will present the study to staff physicians in the Pediatric ED, General Pediatrics, and Pediatric Surgery so they are aware of the study eligibility criteria and how to contact the study team members. Our research nurse will perform daily rounds in the ED and on the wards during clinical rounds to ask and remind the clinical team of any potential participants. The clinical team will ask potential participants if they would like to be approached by research personnel since they may be eligible for the KETODOSE trial. If the patients agree, they will be approached by research staff to check eligibility. Eligibility will then be confirmed with the treating physician or principal investigators, or both. If confirmed, the details of the study will be discussed with the patient and caregiver.

Children and caregivers will be consented and assented for participation in the trial, including the follow-up survey. Once caregivers’ consent and participants’ assent, the research nurse will obtain the drug kit from the ED drug dispensing machine and assign them the drug kit with the smallest subsequent number. Data will be prospectively collected on baseline characteristics, including age, sex, gender, baseline pain severity (vNRS), type of pain, location, and duration of pain and associated symptoms. Following randomization, the study drug kit containing the study drug vials with information on dosing will be administered to the patient by the research nurse or bedside nurse with the clinical research assistant’s help. Each patient will receive a single dose of IV ketorolac and 2 doses of normal saline as outlined in the intervention section above. Time 0 (baseline) will be considered the time at which study drug administration has been completed. Pain assessments will be conducted at 30-, 60-, 90-, and 120-minute intervals following study drug administration. A chart review will be performed approximately one week after the index visit to identify any return visits to the ED and document the reasons for representation, as well as abstract all data regarding other analgesia administered during the enrollment visit.

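### Time to effective analgesia is seen only at scheduled pain scores, so the planned Cox regression needs a grouped-time model or Efron ties; Breslow ties would pull the hazard ratio towards 1

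*Protocol article*

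**What the plan says.** In Table 1 (secondary outcomes, efficacy), the row on time to mild or no pain defines its outcome as "Time to effective analgesia as measured by the time when vNRS of <3 is achieved". It names the analysis as "Cox regression analysis" and gives the hypothesis as "No difference between all ketorolac dosing arms". The list under Secondary Endpoints uses the same event.

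Under Duration of Treatment and Follow-Up, vNRS is taken at baseline and then "at times 30, 60, 90, 120 minutes, and at 6 hours if they are still in the hospital". Secondary Endpoints also lists a 6-hour score. Trial Day-to-Day Operations gives only the first four: "Pain assessments will be conducted at 30-, 60-, 90-, and 120-minute intervals following study drug administration". Nothing in the article describes pain being watched between these times.

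The Primary Objective Analysis Plan names SAS 9.4 as the software. The article does not say how tied event times are handled. It also gives no event rate, hazard ratio or power for this endpoint.

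**The concern.** A child whose pain first falls below 3 between two scores is recorded at the later one, so every event falls on one of four or five times. The usual Cox partial likelihood assumes continuous time with few ties. With many ties, the result depends on the approximation used.

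The Breslow approximation compares each tied event with the full set at risk at that visit, as if none of the other tied children had yet left it. This pulls the estimated hazard ratio towards 1 and makes the standard error too large. Both effects push towards the row's own hypothesis of no difference. In a trial of dose reduction, slower relief on a lower dose would then be harder to see on this endpoint.

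**Working it through.** **Inputs from the article.** 60 children per arm, allocated 1:1:1; scores at 30, 60, 90 and 120 minutes; Cox regression; SAS 9.4.

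**Assumed, because the article gives no figure.** 25-90% of the reference arm reach vNRS <3 by 120 minutes; constant hazard; true hazard ratio (HR) 0.50, 0.60 or 0.67; two-sided 5% test of one arm against another.

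**The plan's own figure.** Only the primary sample size can be reproduced. With SD 1.5, true difference 0.2, margin 1.0, one-sided alpha 0.025 and 80% power, n = 2 × (1.960 + 0.842)² × 1.5² / (1.0 − 0.2)² = 55.2, so 56 per arm by the normal approximation. The noncentral t gives 57 (power 0.806, against 0.799 at 56). Then 57 × 1.05 = 59.85, so 60. The stated 57 and 60 per arm are reproduced, and 60 is used below.

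**How heavy the ties are.** If a proportion F of the reference arm has the event by 120 minutes, the two arms together have 60F + 60[1 − (1 − F)^HR] events. At HR 0.60:
- F = 0.50: 30 + 20.4 = 50.4 events, about 13 per visit.
- F = 0.85: 51 + 40.8 = 91.8 events, about 23 per visit.

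**Where Breslow ties lead in large samples.** At a single visit, the Breslow score equation for two arms is solved by the ratio of event proportions, p1/p0. Under proportional hazards, 1 − p1 = (1 − p0)^HR. With constant hazard and equal spacing, p0 = 1 − (1 − F)^0.25 at every visit, so p1/p0 is the same at each visit and is the limit. At true HR 0.60:

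| F | p0 | p1 | Breslow limit p1/p0 | Shrinkage of log HR |
|---|---|---|---|---|
| 0.25 | 0.0694 | 0.0422 | 0.609 | 3% |
| 0.50 | 0.1591 | 0.0987 | 0.621 | 7% |
| 0.70 | 0.2599 | 0.1652 | 0.636 | 11% |
| 0.85 | 0.3777 | 0.2477 | 0.656 | 17% |

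The last column is 1 − ln(p1/p0)/ln(0.60).

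**Simulation at 60 v 60, true HR 0.60, F = 50/70/85%.**
- Breslow: HR 0.62/0.63/0.66, power 35/48/50%.
- Grouped model (complementary log-log): HR about 0.60, power 42/58/66%.
- Power lost: 7/10/16 points.
- With no true effect, Breslow rejects in 4.2/2.4/1.4% of trials; the grouped model rejects in about 5%.

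**Other hazard ratios (2,000 runs each), F = 50/65/80%.**
- True HR 0.50: Breslow HR 0.52/0.535/0.55, power 59/70/78%; grouped HR about 0.50, power 64/77/87%.
- True HR 0.67: Breslow HR 0.69/0.70/0.71, power 26/29/31%; grouped HR about 0.67, power 30/39/47%.
- At F = 25%, Breslow loses only 3 points of power at HR 0.50 and 1 point at HR 0.67.
- Efron ties give HR 0.49-0.51 at true HR 0.50. Their power is within about 2 points of the grouped model.

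**Adding the 6-hour score.** With an assumed 30% still in hospital, HR 0.50 and F = 65%, Breslow gives HR 0.536 and power 73%, against 0.498 and 80% for the grouped model. The picture does not change.

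**The case against.** The strongest objection is that the article never names Breslow. All the numerical harm comes from that tie method, and tie handling is a detail that a protocol article commonly leaves to the analysis plan. This stands as far as it goes: the omission alone is not an error. What remains is that the article does fix a model, where most of its neighbouring rows say only that a regression will be done. It fixes that model for an outcome that its own schedule makes visit-grouped, and nothing in the article guards against the consequence.

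A reader might infer that Cox regression is the wrong model for these data. The figures do not support that: with Efron ties, Cox does about as well as the grouped model.

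A reader might also infer that a biased result would falsely establish no difference. That goes too far. Even the grouped model has only 42-66% power at HR 0.60, so a non-significant result would not establish equality under either method. The bias is also modest next to the uncertainty. With standard error about 2/√events, it is 0.034 against 0.28 at 50% events and 0.089 against 0.21 at 85%, which is under half a standard error. Under no effect Breslow rejects too rarely, so it does not create false differences.

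Finally, the size depends on an event rate that the article does not give, and at about 25% events there is almost nothing to correct.

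**Conclusion.** The point holds in a limited form. Event times for this endpoint will be heavily tied by design, and the planned Cox regression is sound only if the ties are handled suitably. If Breslow ties were used with 60 per arm and 50-85% of the reference arm reaching vNRS <3, a true HR of 0.60 would be reported as about 0.62-0.66. About 7-16 points of power would be lost, and the test would be conservative.

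These figures rest on the assumed event rates, constant hazard and hazard ratio. A hazard concentrated early would increase the shrinkage: at 90% events, shrinkage of the log HR rises from 19% to 26% at HR 0.50 and from 22% to 30% at HR 0.67.

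The documents do not show that Breslow will be used. The primary conclusion is not touched: it rests on ANCOVA of the 60-minute score, and the sample size was set for that outcome alone. This is a worthwhile improvement to a secondary analysis and not a flaw in the trial.

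**What to change.** State in the analysis plan that time to vNRS <3 is known only to the visit at which it is first recorded. Then choose one of two analyses:
- a discrete-time proportional hazards model: binomial regression on child-by-visit records, complementary log-log link, an indicator for each visit (including 6 hours if that score is used) and treatment arm; or
- Cox regression with Efron ties named explicitly.

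Both keep the hazard-ratio interpretation and use the same data and software. The cost is a sentence or two of text, best settled before the statistician learns which group is which.

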		**Safety**									
			AEs frequency		Frequency of each specific AE related to study drug administration		There will be more AEs associated with standard dose ketorolac compared to low dose regimens		Regression analysis		
**Subgroups**											
		Underlying condition		Proportion of patients with headaches and acute abdominal pain		No subgroup effect is anticipated given prior evidence [35,36]		Regression analysis			
		Sex assigned at birth		Proportion of male, female, and intersex		Differential treatment effect		Regression analysis			
		Gender		Proportions of genders (as defined by participant)		Differential treatment effect for girl or woman compared to boy or man gender.		Regression analysis			
		Age		Dichotomized to 6-11 years vs 12-17 years		Differential treatment effect based on age		Regression analysis			
		Race and ethnicity		Proportion of participants in each race and ethnicity category		Differential treatment effect based on race and ethnicity		Regression analysis			
**Sensitivity analysis**											
		Per-protocol analysis		Completed for the Primary and Safety outcomes		The primary intention to treat analysis results will remain robust		ANCOVA Regression analysis			

^a^Sample size calculation is based on the primary efficacy outcome.

^b^vNRS: 11-point verbal Numerical Rating Scale.

^c^ANCOVA: analysis of covariance

^d^AEs: adverse events.

^e^GEE: generalized estimating equations.

^f^MID: minimal important difference.

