AEs profile analysis: the proportion of children experiencing any AEs as reported by caregivers or health care providers will be compared between groups using logistic regression and presented with their corresponding binomial 95% 2-sided CI. The analysis will evaluate the presence or absence of AEs in each group, such as nausea, epigastric pain, or dyspepsia.

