### Trial Monitoring

Trial conduct will be actively monitored by the study team at McMaster Children’s Hospital. A study coordinator will oversee daily screening, enrollment, data collection, and protocol adherence. Additional monitoring procedures were completed by Hamilton Health Sciences Research Office, including review of REDCap data entry, verification of informed consent, compliance with dosing and outcome measurement protocols, and documentation of any protocol deviations or AEs. Study drug kits will be tracked, and adherence logs will be maintained. Weekly reviews of trial operations are conducted by the principal investigators and study coordinator, and drug accountability will be overseen by the research pharmacy.

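### The only sensitivity analysis that Table 1 states for safety is per-protocol, which poorly suits a harm hypothesis worded by dose received

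*Protocol article*

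**What the plan says.** The per-protocol row under Sensitivity analysis in Table 1 is "Completed for the Primary and Safety outcomes", with the expectation "The primary intention to treat analysis results will remain robust". It is the only sensitivity analysis that the article states for safety.

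The text of the Analysis Plan, part (A), attaches the two sets to the pain endpoint: "The primary analysis will include all participants randomized based on the intention to treat analysis and a sensitivity per-protocol analysis will also be performed". The AE paragraph in the same part says that "the proportion of children experiencing any AEs as reported by caregivers or health care providers will be compared between groups using logistic regression" and names no analysis set. The extension of per-protocol to safety therefore rests on Table 1 alone.

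The hypothesis in the Safety outcome row of Table 1 is "Participants who receive low dose will have fewer AEs than those who receive standard dose".

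On delivery, Trial Day-to-Day Operations states: "Each patient will receive a single dose of IV ketorolac and 2 doses of normal saline". Trial Monitoring covers "compliance with dosing and outcome measurement protocols, and documentation of any protocol deviations or AEs".

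**The concern.** A sensitivity analysis is useful when it tests an assumption that could change the answer. For harms in a dose-comparison trial, the obvious threat is that some children did not get the dose they were allocated, or got something else that can itself cause AEs. A per-protocol set usually handles such children by leaving them out. A child given another arm's dose who then has an AE disappears, although that AE is evidence about the dose actually given.

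The design makes such errors conceivable. Under Interventions, each kit involves three injections drawn under three different dose rules. Under Methods to Protect from Bias, the active and placebo vials look the same and both are labelled as ketorolac. Drawing the wrong volume from the active vial could therefore give a child another arm's dose.

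A second type of deviation also bears on harm. Interventions restricts other NSAIDs for 6 hours after study drug, while Safety Outcomes counts AEs over 8 hours. A child given an NSAID too early would be a natural per-protocol exclusion and would still be inside the AE window.

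At stake is how far agreement between the two safety results can reassure. If the second analysis omits the children in whom dose and harm are hardest to attribute, agreement says little about dose-related harm.

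**Working it through.** The plan states no figure on this point, so there is none to reproduce. The article gives no AE rate and no deviation rate, so everything below is illustrative.

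**Inputs**
- 60 children per arm (Sample Size Calculations).
- Assumed: 3 exclusions per arm. This borrows the 5% in Sample Size Calculations (0.05 × 60 = 3), which is an allowance for withdrawals and not a rate of dosing deviations.
- Assumed: AE rates of 10% (6/60) and 20% (12/60).

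**1. Can a volume error give another arm's dose?** For the 50 kg adolescent used as an example in the Background:
- 0.5 mg/kg, ceiling 30 mg: 0.5 × 50 = 25 mg
- 0.25 mg/kg, ceiling 30 mg: 0.25 × 50 = 12.5 mg
- 0.5 mg/kg, ceiling 10 mg: 25 mg, capped at 10 mg

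The three rules give three different amounts, so applying the wrong rule to the active vial changes the dose group.

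**2. How far can an arm's AE rate move?** With x AEs in 60 children and k excluded, the per-protocol rate runs from (x − k)/(60 − k), if every excluded child had an AE, to x/(60 − k), if none did.

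| Rate with all 60 | All 3 excluded had an AE | None of the 3 had an AE |
|---|---|---|
| 12/60 = 20.0% | 9/57 = 15.8% | 12/57 = 21.1% |
| 6/60 = 10.0% | 3/57 = 5.3% | 6/57 = 10.5% |

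If exclusion were unrelated to AEs, the chance that all 3 excluded children come from the 12 with an AE is C(12,3)/C(60,3) = 220/34,220 = 0.6%. The low end therefore needs deviations and AEs to go together.

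**3. What does one misdosed child do?** Assume 12/60 AEs in a low-dose arm and in the standard arm. Assume also that one of the low-dose children with an AE in fact received the standard dose.
- Grouped by allocation: 12/60 against 12/60, difference 0.
- Per-protocol: 11/59 = 18.6% against 12/60 = 20.0%, difference 1.4 points.
- Grouped by dose received: 11/59 = 18.6% against 13/61 = 21.3%, difference 2.7 points.

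The per-protocol set takes the event away from the low-dose arm but never credits it to the dose that was given. Only the third grouping matches the wording of the hypothesis. One child makes little difference, which also shows how small the issue is if errors are rare.

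**The case against.** The case for leaving Table 1 alone is fair in several respects.

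- **It is only a sensitivity analysis.** The between-group AE comparison stands whatever the per-protocol result. The DSMB also sees AE comparisons by group and is told promptly of related unexpected serious events. This stands and limits the size of the point.
- **The per-protocol set is not defined.** That it drops misdosed or co-medicated children is the usual meaning of the term, not something the article states. This stands as an assumption.
- **Deviations should be few.** There is one supervised dose, and dosing compliance is monitored. This is plausible, and the two groupings may nearly coincide.
- **Bias between arms needs unequal exclusions.** Exclusions with a similar AE mix in every arm would largely cancel in the comparison. This stands too.
- **A per-protocol AE table has a use.** It can show whether disallowed co-medication drives a difference. That is a reason to keep it as a supplement, not to make it the only check.

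A reader might infer three stronger points that the documents do not support. First, that the main AE comparison uses all randomized children, and so counts undosed or misdosed children wrongly: the statement "The primary analysis will include all participants randomized based on the intention to treat analysis" concerns the pain endpoint, and the AE paragraph names no set. Second, that the lack of a named as-treated set is an error: a condensed article commonly leaves this to the full protocol or SAP, which are not shown. Third, that the plan declares the safety result robust: the expectation in Table 1 speaks of the primary intention-to-treat result, although the row covers safety as well.

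**Conclusion.** The point holds in a narrow form and is minor. Table 1 makes a positive choice of per-protocol as the one stated sensitivity analysis for safety. That choice fits poorly with a hypothesis about the dose children receive. A safety population defined in an SAP would not by itself remove the choice.

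The conclusion assumes that per-protocol carries its usual meaning. Its size depends on rates the documents do not give: with 3 of 60 excluded and 12 AEs, the arm's rate could range from 15.8% to 21.1% against 20.0%, and the low end is a worst case. The primary pain analysis, sample size, power and alpha are untouched.

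**What to change.** In Table 1, restrict the per-protocol row to the primary pain outcome. For safety, make the sensitivity analysis one of all children who received any study drug, grouped by the ketorolac dose received, with the logistic model already planned. Keep a per-protocol AE table as a supplement if wanted.

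One rule is needed. The arms' doses coincide at some weights: 0.5 mg/kg reaches 10 mg at 20 kg, so at or below that weight the standard arm and the 10 mg ceiling arm give the same dose; and 0.25 mg/kg reaches 10 mg at 40 kg, where the two low-dose arms meet. A child should therefore leave the allocated arm only when the dose given differs from the one that arm prescribes, and a dose matching no arm should be listed separately.

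The cost is one table cell, that rule and slightly more programming. Monitoring already covers dosing compliance and deviations. The downside is that grouping by dose received departs from randomization for the few misdosed children, so it should stand beside the main AE comparison and not replace it. With 170 of 180 children enrolled when the article was submitted, the change should be dated and made before group identities are revealed to the statistician.
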